### Specific procedure for each of the conditions follows orthopaedic physiotherapy (arthroplasty)

#### Procedures

A database of exercises will be created with different categories and levels of exercises that include range of motion, strength and balance and are subdivided into easy, intermediate and difficult levels. Mobilisation videos (safety with walking frame, mobilising with two elbow crutches and mobilising with one elbow crutch) will also be included. Material on health education and various aspects of their condition and any co-morbidities that they have will also be compiled for dissemination at the appropriate time as determined by the therapist’s interaction with the participants.

At the initial session, a thorough assessment will be carried out by asking the sequence of questions shown in Table 1.

**TABLE 1 T0001:** Assessment questions.

Number	Question
1	How are you doing at home?
2	What is your pain now?
3	How are you mobilising at home?
4	What distance are you managing to mobilise at home?
5	How are your exercises going on at home?
6	What exercises are you doing at home?
7	How are you managing activities of daily living (ADL) such as eating, dressing and personal hygiene activities?
8	What are you struggling with at the moment?

*Source:* [name], [name] & [name], 2020, *Standard operating procedure for the use of telehealth in COVID-19 scenario by physiotherapists at Chris Hani Baragwanath Academic Hospital*, Chris Hani Baragwanath Academic Hospital, Johannesburg.

The framework questions shown in Table 1 will also be translated into Zulu, the language most spoken amongst the study population, and this will form the Arthroplasty Telerehabilitation Patient Notes (Appendix 1). Patients will be asked the questions in the language of choice (English or Zulu). If the patient’s language preference is anything other than English, then a therapist fluent in that language will be the primary person facilitating the telerehabilitation session. This further clarifies why each session will include two physiotherapists because at least one and when possible both physiotherapists will have to be fluent in the patient’s language. Alternatively, a family member will be asked to participate in the telerehabilitation session after getting informed consent, and they will be able to converse with the physiotherapist. The questions will be posed in the patient’s chosen language by the physiotherapist to the patient or family member. The responses will then be translated into English by the other physiotherapist for the purpose of record keeping. Member checking will be performed to validate the responses.

Based on the responses obtained from the patients, a home exercise programme (HEP) with the instructions on how many repetitions and how often to do the exercises will be sent to the patients via their preferred means of communication. To check the accuracy of the patients report on the consistency of performing the exercises, the information will be cross-checked with a family member on obtaining consent from the patient. In addition, the patients will be asked to send a video of them performing one of the exercises prescribed as chosen randomly by the therapist.

At subsequent telerehabilitation sessions (scheduled approximately 3–4 weeks apart), the therapist will obtain feedback on the patient’s functional status at home by using the subjective assessment framework. Follow-up sessions will consist of a re-assessment, patient education including pain management principles, medication adherence, importance of rehabilitation, ensuring that contraindications and precautions are understood and adhered to and scar management. Patient safety will also be addressed by giving suitable advice. Exercises will be prescribed, revised and progressed as required, and patients’ concerns will be addressed. Participant compliance will be monitored by encouraging the patient to keep a rehabilitation diary in which they record their exercises and progress as well as by corroborating the information with the family member. Weekly reminders will be sent, encouraging the patient to continue with their exercise programmes. Once patients have reached their functional goal, they can be discharged.

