Available methods of delivering telerehabilitation services include telephone calls, text messages (SMS or WhatsApp) and emails. Two modes of communication will be used for every participant, and this will be determined by the resources the patient has availed. The participant will initially be contacted via a telephone call, and the concept of telerehabilitation will be explained to them. Informed consent will be obtained from the patient for participation in the research, along with the consent for audio and/or video recordings of the session; therapists are to send or receive video and audio recordings as well as the caregiver to send or receive video and audio recordings should the patient not have a suitable phone. The preferred language of delivery (English or Zulu) will be obtained verbally from the participant prior to proceeding with telerehabilitation services. The mode of delivery of telerehabilitation services will be established at the initial contact. A suitable date and time for each session will be agreed upon between the physiotherapist and the participant. The type of delivery of information and the model of the patient’s phone will guide the extent of information transferred.

The participant and two physiotherapists will be present at each telerehabilitation consultation. Two physiotherapists will be present, as one physiotherapist will provide the telerehabilitation service and the other will record all necessary information, that is, the scribe. The call should therefore be on loudspeaker, in a private office to ensure confidentiality.

Permission will be obtained from the patient to record the session, and it will be an audio recording or video recording depending on how the session is conducted with the patient. The session will be recorded by using a specific app or device. This will be downloaded and stored on Google drive and will be backed up onto an external hard drive. The same will be done for the physiotherapy notes. All will be anonymised and there will be no names or identifying information on the recording.

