### Ethical considerations specifically relating to the paediatric participants

The patient’s caregiver is at liberty to ask questions and seek clarification of the procedures and telerehabilitation in general. The patient’s primary caregiver may at any time ask that the telerehabilitation consultation process be stopped, without future prejudice. An alternative way of safe and ethical follow-up would be considered so that treatment is continued as possible. If the proposed route of telerehabilitation delivery cannot be done because of device or connectivity limitations, the child should still be followed up in other appropriate and safe ways. No videos or images of the child should be sent to therapists on social media platforms.

A ‘form 22’ will be completed in the case of any suspected ‘abuse’, and appropriate and immediate referrals will be made to social services. A copy of this form will be attached to the telerehabilitation recording template. The consulting practitioner’s name as well as the scribe’s name (if applicable) and contact details and location will be recorded. There will be adherence to child protection principles (in the *Children’s Act* 38 of 2005) at all times. The HPCSA guidelines for Privacy and Confidentiality and Protection of Personal Information will be adhered to at all times.

Continuity of care should be facilitated, and practitioners are to ensure that telerehabilitation services meet the same standards of professional, legal, quality and ethical standards as services provided in person. The patient’s caregiver should acknowledge the risks of telerehabilitation consultation in respect of the technology used or assessment made by the practitioner or any physical injury sustained by the child whilst carrying out the HEP. Every effort will be made by the practitioner to mitigate these.

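### When only one of the two physiotherapists speaks the patient's language, the protocol gives the English translation to the other one

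*Protocol article*

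**What the plan says.** The language rule stands in the protocol article, in the Procedures for orthopaedic physiotherapy (arthroplasty). If the patient prefers a language other than English, "a therapist fluent in that language will be the primary person facilitating the telerehabilitation session". For the pair of therapists the minimum is that "at least one and when possible both physiotherapists will have to be fluent in the patient’s language". The questions are put in the chosen language to the patient, or to a relative who has agreed to take part. Then: "The responses will then be translated into English by the other physiotherapist for the purpose of record keeping". The next sentence promises member checking of the responses, and Validity and reliability repeats this. Neither place says who does the check, in which language, or against which record.

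Methods and design sets the roles for every consultation: "one physiotherapist will provide the telerehabilitation service and the other will record all necessary information, that is, the scribe". It also provides for audio or video recording of the session if the patient permits.

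The chronic low back pain section follows a procedure similar to the arthroplasty one. Statistical analysis, item 5, takes the patient-experience themes from an open-ended question within the subjective framework, so from the same conversation.

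**The concern.** The rule names a translator without requiring that this person be able to translate. The fluent therapist is tied to facilitating and the translation is tied to the other therapist, while fluency in both is only preferred. In a session with one fluent therapist, the written English record is assigned to the person less able to follow the answers.

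Any resulting error would fall only on patients who do not use English, so it would differ by language group. The same Procedures section describes Zulu as the most widely spoken language in the study population, so the group concerned is not marginal. The open-ended experience answers are the most sensitive, because their analysis depends on what the patient actually said. The protocol does not ask for the number of fluent therapists to be recorded, so affected sessions could not be picked out afterwards.

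**Working it through.** No figure is stated on this point, so the check is one of logic.

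**Inputs**

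- A: with a non-English preference, the facilitator is fluent (orthopaedic Procedures).
- B: one fluent therapist in the pair is enough; two are preferred (orthopaedic Procedures).
- C: the therapist who is not facilitating translates for the record (orthopaedic Procedures) and is the scribe (Methods and design).
- D: a usable translation needs a translator who understands the language. This is common sense; the protocol does not state it.

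**Cases**

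1. Both fluent. A, B, C and D all hold. There is no conflict.
2. Exactly one fluent, which B permits. By A this therapist facilitates. By C the other one translates. The other one is not fluent, so D fails.
3. A relative takes part. The text has the relative converse with the physiotherapist, but does not say in which language the answers arrive or whether the same person still translates. The conflict is neither removed nor confirmed.

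**Can the sentences be reconciled as they stand?** To keep D in case 2, one of the three rules must give way. Keeping A and C requires two fluent therapists, against B. Keeping A and B requires the facilitator to translate, against C. Keeping B and C requires the non-fluent therapist to facilitate, against A. The translation sentence is not limited to sessions with two fluent therapists, so the protocol does not make this choice itself.

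**Do the stated safeguards reach the English entry?** Member checking would reach it if the entry itself were read back in the patient's language. If the facilitator instead confirms what he or she heard, a faulty entry passes unseen. The text does not say which is done. A recording would allow a later comparison, but it depends on permission, and nowhere is it said to be used for verifying translations.

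**Size.** With *s* the share of sessions held in a language other than English, and *f* the fraction of those with only one fluent therapist, the exposed share of sessions is *s* × *f*. The documents give neither value. The product runs from 0 (if *f* = 0) to *s* (if *f* = 1) and cannot be narrowed from the text.

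**The case against.** The strongest reply is that the text never instructs a non-fluent person to translate. The word itself presupposes understanding, and the sentence works when both are fluent, which is the preferred arrangement. With only one fluent therapist, both are in the same office with the call on loudspeaker, so the fluent one would probably relay the answers. The framework questions are put into Zulu beforehand, the responses are member-checked, and sessions are recorded where permitted. A separate standard operating procedure is also to be developed, and who writes which line could be settled there.

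Much of this stands as a limit on the consequence. A reader might infer that the answers of non-English speakers will be recorded wrongly as a matter of course. The documents do not support that: the problem is confined to sessions with one fluent therapist, and sensible staff would probably find a way round it. But that workaround departs from the stated rule. The article does not leave the task open for the operating procedure to fill; it assigns it, and to the wrong person in a case it permits.

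A reader might also infer that some sessions have no second physiotherapist, because the paediatric ethics section qualifies the scribe's "name (if applicable) and contact details and location will be recorded". That does not follow. The parenthesis concerns the noting of a name, in a paediatric paragraph outside the section that holds the translation rule. Methods and design puts two physiotherapists at each consultation, and Documentation requires the scribe's name without qualification.

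Finally, the named outcome instruments are separate structured tools: HOOS JR and KOOS JR for arthroplasty, and the STarT Back tool, described as available in English and Zulu, for back pain. Caregivers complete their own questionnaire. None of these is shown to be affected, and this part of the objection stands in full.

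**Conclusion.** The point holds in a limited form. In sessions with exactly one fluent therapist, the stated rules assign the English record to a therapist who need not understand the answers, and they cannot all be followed if the translation is to be usable. What is exposed is the notes on the framework questions and the open-ended experience responses of non-English speakers. The safeguards reduce the risk but are not stated to cover the English entry.

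The conclusion rests on reading the other physiotherapist as the one who is not facilitating, which the description of roles in Methods and design supports. The arthroplasty section is covered directly. Extension to the back pain cohort is plausible, because its procedure is described as similar, but this is not spelled out. No percentage of affected records can be defended, since the language most spoken in a population is not the share of patients who choose it for their sessions, and staff fluency is not given. No test, estimate or sample size is shown to change. This is a data-quality correction worth making because it is cheap, and it does not call the study into question.

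**What to change.** Amend the language rule in the arthroplasty Procedures, and the operating procedure that follows from it, as follows.

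- Whoever translates responses into English for the record must be fluent in the patient's language.
- When only one therapist is fluent, that person relays each answer in English to the scribe or writes the English entry, during the call or afterwards from the recording where the patient has permitted one.
- The member check consists of reading that English entry back to the patient in the patient's own language.
- The session sheet records whether one or both therapists were fluent, so that the analysis of themes can show how many records come from each arrangement.

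The cost is revised wording, one extra field on the data sheet and a few minutes of the fluent therapist's time per session. No additional staff are needed, and recording where permitted is already planned.

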#### Outcome measures

The Hip Disability and Osteoarthritis Outcome Score Joint Replacement (HOOS JR), which is a self-reported questionnaire on performance pain and functional status, with good reliability and construct validity, will be used for patients with hip arthroplasty (Lyman et al. 2016). The Knee Injury and Osteoarthritis Outcome Score (KOOS JR) will be used for knee arthroplasty patients. The KOOS JR is a knee-specific outcome measure assessing pain, symptoms and function related to their knee and associated problems (Lyman et al. 2016). The KOOS has been validated in multiple populations, activity levels and ages. Divergent and convergent construct validities have been determined when comparing to the SF-36 a health survey. The HOOS JR and KOOS JR will be used as an objective outcome measure for participants with arthroplasty.

### Outpatient chronic low back pain physiotherapy specialist area

#### Procedures

The sample will consist of participants who had been assessed as being suitable for group exercise classes, after having completed individual face-to-face physiotherapy sessions. A similar procedure as for arthroplasty telerehabilitation session will be followed for the above cohort of patients. The telerehabilitation session will follow an adapted framework of questions, which will explore the patient’s functional ability, pain score and self-management principles (Appendix 2). At every session, the Keele STarT Back screening tool will be used as the outcome measure to monitor patient progress and to categorise patients as low, medium and high risk.

Following the first session of telerehabilitation, those patients who fall into the high-risk category will be called back for a face-to-face consultation session and managed accordingly. Patients who fall into the medium- and low-risk category will be managed via telerehabilitation, wherein a specific category or level of a HEP will be prescribed and sent to the patients via their preferred method of communication. Follow-up appointments will be at 2–4-week intervals. Based on the patients’ report and presentation, exercises and advice will be progressed. Once patients have reached a score of less than three on their Keele STarT Back screening assessment tool, they can be discharged from physiotherapy.

#### Outcome measure

The Keele STarT Back screening tool is available in English and Zulu, and according to Bruyère et al. (2014) the test-retest reliability of the Keele STarT back screening tool total score was excellent with an intraclass correlation coefficient of 0.90. The validity was found to be moderate to high in Pearson’s correlation for questions three to nine and a low correlation for questions one and two (Bier et al. 2017). This tool is designed to screen primary care patients with low back pain and serves as a prognostic indicator for initial decision-making. This tool allows clinicians to group low back pain patients into three categories of risk.

### Paediatric physiotherapy speciality area

#### Procedures

The population for paediatrics will comprise children with cerebral palsy, developmental delay and acute orthopaedic conditions. A resource survey (Appendix 3) will be used to determine suitable participants for conducting telerehabilitation services. The main telerehabilitation SOP will thereafter be followed. In addition, because minor children are being treated, informed consent and assent will be obtained from the child participant as well as the primary caregiver depending on the age of the child. The telerehabilitation consultation will include a thorough subjective clinical assessment in accordance with the Subjective Framework Questions (Appendix 4).

Based on the assessment obtained from the participant, a HEP will be selected for the patient from the database. The database will contain videos and images of relevant physiotherapy interventions related to the conditions within the paediatric unit, based on various ages and developmental levels. These resources will be accompanied by basic inputs from speech and language therapy (SLT) and occupational therapy (OT). A section on general advice and health education information will also be included. The participant or primary caregiver will then be sent the links or material via their preferred mode of communication. Based on the information received and the therapist’s clinical reasoning, additional information may be included, for example, verbal advice on the progression of a safe HEP, usage/repair/re-ordering of assistive devices/orthotics and on the need to consult specialist doctors, dieticians, social services, psychiatry and other rehabilitation professionals. Initial appointments will be scheduled every 2–3 weeks, and subsequent consultations will be scheduled every 5–6 weeks.

At each follow-up session, the following will be obtained: feedback from the caregiver on the patient’s functional status, the response of the child to the HEP and feedback/concerns from the caregiver, by using the Subjective Assessment Framework. Based on the caregiver’s report, the HEP and advice will be progressed accordingly and referrals made. At the final consultation as determined by the condition of the patient, caregivers will be requested to provide feedback on their perceptions and experiences of telerehabilitation (Appendix 5). If less than satisfactory outcome with telerehabilitation is received, face-to-face sessions will be considered as an alternative to telerehabilitation. Once patients have reached their functional goal, they can be discharged. Feedback from the therapist on the telerehabilitation experience will be collected as shown in Appendix 6.

### Documentation

The following processes will be followed to ensure participant safety, accurate documentation and consistency of procedures:

The date, duration and time of the telerehabilitation session must be recorded as part of the patient’s notes.It must be clearly stated that assent and/or consent for telerehabilitation was obtained from the patient and caregiver or parent.The patient and/or caregiver must clearly express their understanding and confirm that he or she agrees that the practitioner or therapist may engage via a telerehabilitation consultation.That the patient and/or caregiver understand(s) that the consultation will be done via telephone/video/the Internet conferencing technology and that he or she agrees thereto.The purpose of the telerehabilitation consultation is to assess and treat his or her condition, subject to the information provided by the patient and/or caregiver.Ensure detailed clinical record keeping for the session – in Subjective, Objective, Assessment and Plan (SOAP) format document findings. All findings will be based on information provided by the patient and/or caregiver.If a standardised outcome measure was used, this should be included in the patient’s records.The consulting practitioners name, the scribe’s name and the location of the session must be documented at the end of the records (HPCSA 2014).

